### Objectives

The primary objective is to:

Assess the feasibility, acceptability and reliability of the CAP questionnaire and clinical QST to identify people at risk of persistent and/or worsening pain arising or augmented by augmented central pain processing across a range of musculoskeletal pain conditions.Determine the ability of the clinical QST and CAP questionnaire, alone or combined, to predict persistent and/or worsening pain at 6 and 12 weeks.Determine the ability of clinical QST and CAP alone or combined with other proxy measures of augmented central pain processing, demographics and clinical variables to improve prediction of persistent and/or worsening pain at 12 weeks.Validate clinical QST and CAP in relation to laboratory QST as an outcome measure for augmented central pain processing.Evaluate associations between the risk tool (clinical QST and CAP) and key patient-centred outcomes linked to augmented central pain processing.

The secondary objectives are to:

Determine the ability of the clinical QST and CAP questionnaire, alone or combined, to predict persistent and/or worsening pain at 6 and 12 weeks.Determine the ability of clinical QST and CAP alone or combined with other proxy measures of augmented central pain processing, demographics and clinical variables to improve prediction of persistent and/or worsening pain at 12 weeks.Validate clinical QST and CAP in relation to laboratory QST as an outcome measure for augmented central pain processing.Evaluate associations between the risk tool (clinical QST and CAP) and key patient-centred outcomes linked to augmented central pain processing.

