### Outcomes

Primary outcomes:

The risk for persistent pain or pain worsening to a clinically important extent, using the risk stratification tool (combined clinical QST and CAP).Sensitivity and specificity of the risk stratification tool to identify people at risk of persistent and/or worsening pain.

Secondary outcomes:

External validity of the risk stratification tool against laboratory QST and validated questionnaires addressing central sensitisation-related characteristics.Internal validity of the risk stratification tool.Pain prognosis: Prediction of pain at 12 weeks by the risk stratification tool, CAP and clinical QST separately.Mechanistic underpinning: Investigate, according to the assessments outlined, which pain mechanisms contribute to risk levels identified using the risk stratification tool.Acceptability and feasibility of the risk stratification tool by patients, healthcare professionals (HCPs) and researchers within both research and clinical environments.Refinement of the risk stratification tool by patients, HCPs and researchers.Inter-rater and intrarater reliability of the risk stratification tool.

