**Figure 1 F1:**
[figure not shown]
CONSORT (Consolidated Standards of Reporting Trials) participant flow diagram. CAP, Central Aspects of Pain; NHS, National Health Service; PIS, Participant Information Sheet; T0, time 0 (baseline); T1, time 1 (6 weeks); T2, time 2 (12 weeks).

The combined tool will include the CAP questionnaire and clinical QST modalities, replicating laboratory QST using low-cost equipment currently available within the UK National Health Service (NHS) (table 1). The CAP questionnaire^35 36 38 39^ has been selected because it was developed based on the current mechanistic understanding of augmented central pain processing and the potential patient-reported effects. CAP includes eight items strongly associated with QST in musculoskeletal pain.^38^ It displays excellent psychometric properties, is feasible, patient-acceptable and can predict pain prognosis in musculoskeletal conditions so far investigated.^35^,^3751^

**Table 1 T1:** Laboratory versus clinical QST assessments for pain hypersensitivity

Modality	Laboratory	Clinical
**Pressure Pain Detection Threshold (PPT**) **Protocol:** Pressure is increased at 50 kPa/s until the sensation of pressure changes to pain^53^ **Test sites:** non-dominant brachioradialis	**Equipment:** Pressure algometer (Algomed, Medoc) 1 cm^2^ tip	**Equipment:** Handheld dynamometer (Wagner Force Ten) 1 cm^2^ tip
**Temporal Summation of Pain** **Protocol:** apply single stimuli, apply 10 stimulations at 1/s and rate pain/sharpness after 1 and 10 **Test sites:** dominant brachioradialis	**Equipment:** Pinprick stimulator (256 mN pinprick)	**Equipment:** Von Frey Filament (256 mN)
**Conditioned Pain Modulation** **Protocol:** PPT is performed preconditioning and postconditioning. Conditioning: A blood pressure cuff will be inflated until the distal radial pulse cannot be palpated. Participants are then asked to squeeze a ball until pain reaches 4/10. **Test sites:** non-dominant brachioradialis	**Equipment:** Blood pressure cuff, pressure algometer (Algomed, Medoc)	**Equipment:** Blood pressure cuff, handheld dynamometer 1 cm^2^ tip (Wagner Force Ten)

QST, quantitative sensory testing.

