QST will be assessed on the brachioradialis muscle belly 5 cm from the lateral epicondyle^52^ of the dominant (PPT, CPM) and non-dominant arm (TSP), and the volar forearm of the dominant arm (Heat Pain Threshold (HPT), Offset-analgesia) (figure 2). Each laboratory and clinical QST protocol test will be undertaken in a standardised order (PPT, TSP, CPM, HPT, then offset analgesia). The order of laboratory and clinical QST will be randomised to minimise the potential for sequential effects to confound comparisons between the two modalities. These measures have previously been well tolerated by individuals with musculoskeletal pain and will be conducted regardless of their pain status.

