Using the Advanced Pain Discovery Platform CPM protocol, PPT will be measured before and after a pain-conditioning stimulus. The unconditioned stimulus will be the average of three trials on the non-dominant brachioradialis muscle. A 15 cm wide pressure cuff on the dominant forearm will be inflated to occlude arterial blood flow. Participants will be asked to squeeze a stress ball until they indicate pain levels of 4/10 (0=no pain, 10=worst pain imaginable) due to ischaemic pain,^56^ at which point PPT is performed again before the cuff is released. The CPM effect will be calculated as the mean of three unconditioned PPT minus the conditioned PPT.^56^ Thus, negative values indicate an inhibitory CPM effect and positive values a facilitatory effect.^56^ To account for measurement error, the within-participant coefficient of variation (CoV) of the unconditioned PPT will be determined; only the CPM effect greater in magnitude than the CoV will be considered a true response.^57^

HPT will be assessed using a 6.6×4×4.4 cm probe (TCS II, QST.Labs, France) applied to the non-dominant volar forearm. To overcome adaptation or sensitisation, the forearm is divided into four zones (figure 2), with the probe moved from zone to zone between stimuli.^58^ The method of limits will be used to establish the heat thresholds. A computer-controlled heat stimulus will be applied, with the baseline temperature set at 32°C and increasing at a rate of 1°C/s to a maximum of 50°C.^57^ The participant will indicate using a handheld button when the sensation of heat changes to one of pain, at which point the test is stopped. HPT is calculated as the mean of three replicates taken 10 s apart. Lower HPT values indicate greater sensitivity to thermal pain.

Offset analgesia will be measured using a tonic heat stimulus train to the skin of the non-dominant volar forearm (figure 2). The study temperature will be individualised. Starting at baseline (32°C), the first temperature will be set to HPT for 10 s, then returned to baseline and increased by 1°C. The participant will continuously rate their pain on an electronic VAS (eVAS). When the eVAS reaches 50/100, the test will be stopped^58^ and the actual temperature recorded. Pain^50^ will be determined as the average of two trials separated by 1 min. To ensure the tonic heat stimulus is noxious for the offset analgesia protocol, the following rule will apply:

Pain^50^<45°C then tonic heat stimulus=Pain^50^+2°C.

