### Data analysis

Pain profiling will be undertaken irrespective of condition. Multivariate modelling (principal component analysis, cluster analysis or latent class analysis) to identify distinct pain patterns.Between-group comparisons (eg, independent T-tests, Mann-Whitney U) will explore between pain profile comparisons.Associations between pain profiles and clinical outcomes (eg, pain intensity, pain-related worrying, disability, quality of life) will be examined.Sensitivity analysis will be conducted between diagnostic groups and between matched samples.We believe that QST will identify somatosensory pain profiles, while CAP will identify psychological hypervigilance pain profiles, each associated with augmented central pain processing. Using the pain profiles combined with pain at 12 weeks, we will identify any relationship between potential augmented central pain processing and pain prognosis at 12 weeks (eg, persistent/worsening pain, pain>patient acceptable symptom state), informed by patterns of pain over 12 weeks and knowledge.Pain prognosis: Bivariable correlations will identify and permit comparison between baseline factors significantly associated with 3-month pain prognosis. Separate multivariable models will determine whether the CAP questionnaire, clinical QST or laboratory QST can increase prognostic precision beyond other clinical and demographic variables significantly associated with pain prognosis. Multivariable modelling will define whether and which combination of the CAP questionnaire and QST importantly improves prognostic determination. The proportion of the prognosis explained by each and by both the CAP questionnaire and clinical or laboratory QST will be determined.The reliability and validity of the stratification tool (combined CAP and clinical QST) will be tested across the study population, with sensitivity analysis conducted across the diagnostic groups, age, sex, social and ethnic strata.Test–retest reliability will be assessed using intraclass correlation between repeated CAP questionnaires and between two raters for simplified clinical QST.RMT, Cronbach’s alpha and confirmatory factor analysis will evaluate internal validity, consistency and factor structure. If multiple constructs with significant residual values exist, this will be further explored using principal component analysis of residuals, the eigenvalue criterion, residual correlations and theoretical understanding.Correlation analysis will assess external validity against self-reported questionnaires and laboratory QST.Mechanistic underpinning: The dataset will be randomly divided into development and validation sets. Exploratory and confirmatory factor analyses will determine whether there are subgroups of the population for whom the stratification tools function differently. Correlations between CAP scores and clinical and laboratory QST indices of augmented central pain processing will be identified. Bivariate and multivariable models will ascertain whether associations may be explained by one or more characteristics linked to maladaptive pain processing (sleep disturbance, fatigue, anxiety, depression, cognitive impact, catastrophising).Relevance to patient-centred outcomes: Bivariate associations between CAP or QST and patient-reported outcome measures scores will be determined through linear regression. The proportion of participant-reported pain or other patient-reported outcome measures explained by CAP scores, clinical and/or laboratory QST measures, will be identified as R^2^ in multivariable regression.Qualitative data will be analysed using reflexive thematic analysis following the stages outlined by Braun and Clarke.^97^ A reflexive journal will be kept throughout the data collection process. Data will be coded inductively primarily, while also being informed by the Normalisation Process Theory^90 91^ commonly used to support evaluation in health interventions and inform the tool’s theoretical acceptability and feasibility. A ‘critical friend’^98^ will code a sample of transcripts independently until consensus is reached. After the consensus is reached, all remaining transcripts will be coded. NVivo V.15 will assist in managing, analysing, and visualising the qualitative data set. A thematic map may also visually represent the main themes developed.

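### Clinical QST is compared with laboratory QST by correlation alone, which can support convergent validity but cannot show that the two versions agree

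*Protocol article*

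**What the plan says.** Objectives includes the aim "Validate clinical QST and CAP in relation to laboratory QST as an outcome measure for augmented central pain processing". Outcomes lists, as a secondary outcome, "External validity of the risk stratification tool against laboratory QST and validated questionnaires addressing central sensitisation-related characteristics".

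Experimental procedures describes the clinical modalities as "replicating laboratory QST using low-cost equipment currently available within the UK National Health Service (NHS". Table 1 gives each modality a single protocol and test site for both versions, with the same tip area for PPT and the same nominal 256 mN force for TSP. The Discussion repeats that the clinical measures keep to the laboratory protocol. The text and Table 1 differ on which arm is used for each test, but in each place both versions share one site, so that does not affect this point.

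The two versions are not identical in procedure. In the PPT description, the participant ends the laboratory test with a button and the clinical test by saying stop.

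On design: "The order of laboratory and clinical QST will be randomised to minimise the potential for sequential effects to confound comparisons between the two modalities".

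On analysis, the only method named for the direct comparison is: "Correlation analysis will assess external validity against self-reported questionnaires and laboratory QST". An agreement-type statistic is named in the same section, but for other pairs of measurements: "Test–retest reliability will be assessed using intraclass correlation between repeated CAP questionnaires and between two raters for simplified clinical QST". Both QST versions also enter prognostic modelling: "Separate multivariable models will determine whether the CAP questionnaire, clinical QST or laboratory QST can increase prognostic precision".

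**The concern.** CAP and the questionnaires measure different constructs on different scales, so correlation is the natural tool for them. Clinical and laboratory PPT, TSP and CPM are different: each pair is meant to be the same quantity in the same units. The useful question is then how far the two readings differ within a person, both on average and in spread. Correlation answers only whether people are ranked similarly along a straight line, and it also depends on how varied the sample is.

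A consistent offset or a scale error between the devices would therefore not show up in the planned comparison. An offset is plausible for PPT because the stopping action differs. What is at stake is the wording of the conclusion: a high correlation could be read as showing that the low-cost version can replace the laboratory one, which it would not establish.

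**Working it through.** **Plan's own figure.** There is none to reproduce. The article states no expected correlation, acceptance threshold, limits of agreement or sample size for this comparison. All effect sizes below are assumptions. Only the 250 baseline participants and the 50 kPa/s ramp come from the article.

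**1. What correlation misses.** Let the laboratory value have SD 1 and let the clinical value have true correlation ρ with it, scale factor s and offset b (in laboratory SDs). Pearson r equals ρ for any b and any positive s. Lin's concordance coefficient is CCC = 2ρs / (1 + s² + b²).

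| ρ | b | s | Pearson r | CCC |
|---|---|---|---|---|
| 0.9 | 0 | 1 | 0.90 | 1.8/2 = 0.90 |
| 0.9 | 0.5 | 1 | 0.90 | 1.8/2.25 = 0.80 |
| 0.9 | 1 | 1 | 0.90 | 1.8/3 = 0.60 |
| 0.9 | 0 | 1.5 | 0.90 | 2.7/3.25 = 0.83 |
| 0.8 | 0.5 | 1 | 0.80 | 1.6/2.25 = 0.71 |
| 0.8 | 1 | 1 | 0.80 | 1.6/3 = 0.53 |
| 0.8 | 0 | 1.5 | 0.80 | 2.4/3.25 = 0.74 |

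A simulation of 200,000 pairs per setting gave the same values to within 0.01.

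**2. Which modalities are exposed.** If a device reads a + k × (true value):
- PPT carries both a and k.
- TSP is the rating for the repeated stimuli minus the rating for the single stimulus, so a cancels and k remains.
- CPM is also a difference: "The CPM effect will be calculated as the mean of three unconditioned PPT minus the conditioned PPT". Again a cancels and k remains.

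So an offset is a PPT matter, while a scale error concerns all three.

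**3. A plausible PPT offset.** At 50 kPa/s, each extra 0.1 s between the pain threshold and the end of loading adds 50 × 0.1 = 5 kPa. If saying stop and the assessor's reaction took 0.5 s longer than the button (assumed), the clinical reading would be 25 kPa higher. With an assumed laboratory SD of 120 kPa, b = 25/120 = 0.21. At ρ = 0.9, CCC = 1.8/(2 + 0.043) = 0.88 against 0.90 with no offset. A single coefficient barely registers a bias of this size, so mean bias should be reported as well.

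**4. Can the study estimate it?** The SD of paired differences at ρ = 0.9 is √(2 × 0.1) × 120 = 54 kPa. With 250 pairs, the 95% half-width for mean bias is 1.96 × 54/√250 = 6.7 kPa. At ρ = 0.8 it is 1.96 × 76/√250 = 9.4 kPa. A 25 kPa offset would be clear in either case. The 95% limits of agreement at ρ = 0.9 lie 1.96 × 54 = 105 kPa either side of the bias, a spread that r = 0.90 does not convey.

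**5. Role of test order.** Suppose the second battery shifts by d SD in either order, with order randomised 1:1. The mean device difference stays at zero, and r becomes (ρ − d²/4)/(1 + d²/4). At ρ = 0.9 and d = 0.3 this is (0.9 − 0.0225)/1.0225 = 0.86. For limits of agreement, at ρ = 0.8 the variance of differences is 2 × 0.2 = 0.40, and an unmodelled shift of ±0.3 adds 0.09, or 22.5%. Leaving order out therefore lowers r and widens the limits; it does not conceal bias.

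**The case against.** The strongest reply is that the sentence concerns external validity of a combined CAP-plus-QST tool. That tool has no unit in common with laboratory PPT, so limits of agreement cannot apply to it, and correlation is a usual method for convergent validity. This stands for the combined tool, CAP and the questionnaires. It does not cover the per-modality comparison, where the article itself claims replication and where no other direct method is named.

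A second reply is that analysis detail belongs in the SAP. That is fair for an order term: the article randomises order as a design safeguard and neither includes nor excludes order from the analysis. It is weaker for the main point, because the article does name a method, and names intraclass correlation for other pairs.

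Some stronger readings are tempting but not supported:
- *Ignoring order could let a biased device be declared valid.* Unmodelled order attenuates r, which makes a good result harder to reach. The article states no threshold or rule for declaring validity.
- *Only the device differs.* The PPT stopping action differs too.
- *Laboratory cut-offs would misclassify patients.* With an assumed mean of 300 and SD of 120 kPa, the lowest-quarter cut-off is 300 − 0.674 × 120 = 219 kPa. A clinical device reading 20% low (mean 240, SD 96) would put Φ(−0.22) = 41% below it. The article plans no such transfer, and a tool calibrated on clinical readings would not suffer from a constant or proportional bias.
- *Carry-over is unequal because the laboratory battery ends with heat tests.* The Abstract and Table 1 suggest that heat is laboratory-only, but the article describes no resulting shift, and the heat tests are on the volar forearm. This remains an inference.

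**Conclusion.** The point holds in a limited form. For the direct comparison of clinical with laboratory PPT, TSP and CPM, the article fixes correlation only. That can support convergent validity. It cannot support a conclusion that the two versions give interchangeable readings, because an offset (chiefly in PPT) or a scale error (in any of the three) would go undetected.

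The size is unknown, since the article provides no data on bias. The illustrations rest on assumed correlations of 0.8 and 0.9, assumed biases and an assumed PPT SD of 120 kPa; the 41% and 22.5% figures in particular are illustrations only. The prognostic comparison of the two versions is unaffected by a constant or proportional bias, and the outcome concerned is secondary. This is an inexpensive improvement to the analysis and does not threaten the study's main prognostic results.

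**What to change.** For each paired modality (PPT, TSP, CPM), report alongside the correlation:
- the mean clinical-minus-laboratory difference with its 95% confidence interval and 95% limits of agreement (log scale for PPT if the spread grows with the level);
- an absolute-agreement ICC or concordance coefficient;
- a paired model with device and randomised battery order as factors.

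If agreement is not to be assessed, state that the comparison addresses convergent validity only and draw no conclusion about interchangeability. Keep correlation for CAP, the questionnaires and the combined tool.

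The cost is a short addition to the analysis plan and some analysis time. Both measurements are already planned on the same participants and the order is already randomised, so no further assessments or participants are needed.

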
## Ethics and dissemination

The University of Nottingham sponsors the study (Sponsor reference 24030). Ethical approval was granted by the Yorkshire & The Humber—South Yorkshire Research Ethics Committee, reference number: 24/YH/1062, protocol version 1.0, 13 Jun 2024. The trial was prospectively registered on 23 July 2024 (ClinicalTrials.gov NCT06518278).

The protocol and results will be submitted for publication in open-access, peer-reviewed scientific journals and presented at leading international and national conferences, including the Arthritis UK Pain Centre scientific and educational meetings, to inform research and clinical practice. Lay summaries of the findings will be developed in partnership with our lived experience research partners and the Arthritis UK Pain Centre Patient and Public Advisory Group. The findings will also be posted on the established Arthritis UK Pain Centre website and presented at annual stakeholder engagement events. We will collaborate with the Communications Teams at the University of Nottingham and Arthritis UK to disseminate findings through media releases and public engagement activities.

## Discussion

The clinical evaluation of how augmented central pain processing contributes to musculoskeletal pain currently needs to be standardised and undertaken more frequently to help determine more effective treatments. There is an urgent need for robust, standardised assessment. This study combines a simple self-reported questionnaire (CAP) with clinical QST to optimally identify those at risk of poor pain outcomes likely due to augmented central pain processing. Such a tool would be valuable in clinical settings, where it could identify individuals who may benefit from specific, targeted treatments. Follow-up interviews with participants, HCPs and researchers will further our understanding of the feasibility and usefulness of the proposed risk stratification tool in clinical and research settings and aim to reduce barriers to implementation.

Various augmented central pain processes arise at different times and intensities within an individual. QST and questionnaires are intended to capture psychophysical and higher-order pain processing, respectively, each accounting for a small proportion of the other’s variance. Combining these tools, rather than using them in isolation, may offer a clearer understanding of the likely mechanistic underpinning of augmented central pain processing and improve the ability to identify individuals at risk of poor outcomes likely due to augmented central pain processing. By integrating QST protocols, which mimic laboratory measures and utilising low-cost equipment currently available in healthcare settings, plus combining the quantitative data with interviews to assess the tools’ acceptability, usability and real-world applicability, we aim to ensure implementation in clinical practice. If implemented in clinical practice, the risk stratification tool could assist in diagnosing, measuring, and evaluating treatment for individuals with a range of chronically painful musculoskeletal conditions.

The risk stratification tool will undergo rigorous psychometric testing to establish its validity in predicting the risk of persistent or worsening pain, likely due to augmented central pain processing, in individuals with inflammatory arthritis, osteoarthritis, chronic low back pain, or fibromyalgia. Recruiting across a range of musculoskeletal conditions enhances the generalisability across common pain conditions. We anticipate that a single tool may be valid across chronic musculoskeletal conditions, based on the premise that different musculoskeletal conditions share the same augmented central pain processes and pain prognosis.^5^ Sensitivity analysis will determine whether the risk stratification tool behaves the same, regardless of the condition(s). We will assess the predictive capabilities of the risk stratification tool individually and determine whether the combined stratification tool is more effective than CAP, clinical or laboratory QST.

The current study uses QST modalities to assess augmented central pain processing in musculoskeletal pain. The qualitative data will refine the risk stratification tool to ensure it is feasible and acceptable for clinical practice within the patient population. We will examine the current barriers to assessing and measuring maladaptive pain processing in clinical practice. This mixed-methods approach will enable us to develop a risk-stratification tool that is likely to be more easily implemented in clinical practice. The risk stratification tool will also facilitate the evaluation of novel and existing treatments for efficacy in homogeneous clinical populations at the highest risk of poor pain outcomes.

Augmented central pain processing occurs in a multidimensional manner. We have selected laboratory QST measures that have been published and validated to serve as proxy measures of pain processing. For each clinical measure, we have adhered to the standardised laboratory protocol, employing low-cost equipment currently available in clinical practice. While we have incorporated as many QST modalities as possible, some, such as vibration or thermal grid illusion, have not been included due to a lack of equipment or the development of new techniques during the study. This suggests that, as equipment and measures continue to develop, the tool may need later refinements. The risk stratification tool will be assessed only once in the study and is not designed to evaluate changes in augmented central pain processing over time. At present, it remains unclear when a change in augmented central pain processing without intervention may occur. The mechanistic understanding and outcome measurement of pain are rapidly advancing, yet remain incomplete. Changes in understanding and the development of new indices of augmented central pain processing may justify adapting the tool we aim to develop. No tool should be regarded as definitive. There is potential for interactions, such as synergy, that may complicate interpretation. It has not been possible to address this without adequately validated and easy-to-apply tools and paradigms to measure nociceptive contributions to pain across diagnostic groups.
